#### Descriptive statistics

Baseline characteristics will be presented as mean ± SD or median (range) for continuous data and as numbers with corresponding percentages for categorical data as appropriate. Comparisons between randomized groups will be analysed using X^2^ or Fisher’s exact test for categorical variables and the Student T-test or Mann-Whitney U test for continuous variables, with normality verified by the Shapiro-Wilk test and histograms.

#### Primary study parameter

Differences between IKDC 2000 at baseline and one-year post-operative will be determined for each group, as well as differences between the groups at each follow-up. In case of clinically meaningful differences between groups (> 10 points on the IKDC2000), the non-inferiority hypothesis will be rejected. In case of non-inferiority, superiority analyses will be conducted. For normally distributed data mixed models analyses for repeated measures will be used. In case of non-normally distributed data, the Friedman test for differences within groups, and Mann-Whitney Y test for differences between groups, will be used. A distinction will be made between short term (6 weeks, 3, 6, 9 months and 1 year), mid-term (2 and 5 year) and long-term (10 year) postoperative outcomes.

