### Main study parameter/endpoint

The primary objective of this non-inferiority study is to determine whether ACL repair will result in at least equal effectiveness compared with ACL reconstruction in terms of the self-reported functional outcome measured by the International Knee Documentation Score 2000 subjective knee evaluation score (IKDC Subjective) 1 year postoperative (Table 1) [23–25].

**Table 1 Tab1:** Oversight of the investigations and follow-up moments

	B	OR	6w	3 m	6 m	9 m	1y	2y	5y	10y
X-ray	x	x					x	x	x	x
MRI	x									
IKDC 2000 Subjective	x		x	x	x	x	x	x	x	x
IKDC 2000 Current health	x	x	x	x	x	x	x	x	x	x
IKDC 2000 History	x	x	x	x	x	x	x	x	x	x
IKDC 2000 Demographic form	x	x	x	x	x	x	x	x	x	x
IKDC Physical examination	x		x	x	x	x	x	x	x	x
KOOS	x		x	x	x	x	x	x	x	x
Tegner score	x		x	x	x	x	x	x	x	x
VAS satisfaction	x		x	x	x	x	x	x	x	x
AP laxity	x		x	x	x	x	x	x	x	x
LSI power tests	x				x	x	x	x	x	x
LSI jump tests					x	x	x	x	x	x
Sport specific fatigue test							x			
Concomitant injury		x								
Rupture pattern		x								
Quality repair		x								
Complications & side effects		x	x	x	x	x	x	x	x	x
Re-rupture			x	x	x	x	x	x	x	x

*B* baseline, *OR* peri-operative, *w* weeks, *m* months, *y* years, *IKDC* International Knee Documentation Score, *KOOS* Knee Injury and Osteoarthritis Outcome Score, *VAS* Visual Analog Scale, *AP* anteroposterior, *LSI* leg symmetry index

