### Sample size determination

In order to detect non-inferiority of ACL repair compared to ACL reconstruction surgery in terms of patient self-reported functional outcome measured by the IKDC Subjective score, to achieve a power of 90% and an alpha of 5%, a sample size of 20 patients in each study group is required. According to literature, it seems relevant to consider a standard deviation at nine in both groups [36]. A difference of 11, 5 points in score of IKDC 2000 is suggested as clinically relevant [37]. The margin of equivalence 10 lies within this clinically relevant effect size.

Considering a lost-to-follow-up rate of 20%, it is planned to include 24 patients per randomization group. Thus, in total 48 patients will be included in the study.

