To our knowledge, this is the first randomized controlled trial to investigate the functional recovery after ACL suture repair in comparison to ACL reconstruction. This trial has the potential to demonstrate, with a good level of evidence, the effectiveness of ACL suture repair combined with dynamic augmentation as well as microfracture of the femoral notch compared to the gold standard ACL reconstruction using autologous hamstring. As it is not yet clarified what the exact indications for this procedure are and in order to minimize the possible influence of confounding factors on the effectiveness of repair or reconstruction, patients suffering from severe common concomitant injury in ACL rupture, i.e. large meniscal injury needing repair or cartilage injury requiring surgical intervention, were excluded in the current study. Despite the fact that it might limit the generalisability of our findings, it does provide a higher intrinsic validity. If proven at least equally effective, ACL suture repair with dynamic joint bridging stabilisation can be considered as an innovative treatment for ACL ruptures.

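### The non-inferiority decision rule attaches no confidence limit or alpha to the 10-point margin, although the sample size is built on a formal test against it

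*Protocol article*

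**What the plan says.** The Primary study parameter section, under Statistics in the protocol article, states how non-inferiority is judged: "In case of clinically meaningful differences between groups (> 10 points on the IKDC2000), the non-inferiority hypothesis will be rejected". It continues: "In case of non-inferiority, superiority analyses will be conducted". No other sentence in the article says how the primary question is decided, and no confidence interval is mentioned anywhere.

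The same section then lists methods. "For normally distributed data mixed models analyses for repeated measures will be used"; otherwise a Friedman test within groups and a Mann-Whitney test between groups. None of these is linked to the 10 points.

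Sample size determination treats the question as a formal test: "to achieve a power of 90% and an alpha of 5%, a sample size of 20 patients in each study group is required". It uses an SD of 9 in both groups and a margin of 10, cites 11.5 points as clinically relevant, and raises 20 to 24 per group for 20% loss. It does not say whether alpha is one-sided or two-sided, nor what true difference was assumed.

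The aim in Main study parameter/endpoint has one direction: "The primary objective of this non-inferiority study is to determine whether ACL repair will result in at least equal effectiveness compared with ACL reconstruction", measured by the IKDC Subjective score 1 year after surgery.

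**The concern.** A non-inferiority claim needs evidence that excludes a deficit as large as the margin. That evidence is a confidence limit, or an equivalent one-sided test, compared with the margin. The written rule asks only whether a difference exceeds 10 points and names no allowance for sampling error. The alpha used to size the trial then plays no part in the decision, and the two sections describe different procedures.

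This sentence produces the trial's main answer. The Discussion says what follows from a favourable result ("If proven at least equally effective"): repair could then be considered as an innovative treatment. Under the literal rule an observed deficit of 9 points would support that conclusion, although the data would be compatible with a deficit well beyond the margin.

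A lesser drafting flaw is that the sentence speaks of differences between groups without saying which group must not be worse.

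**Working it through.** **Inputs.** From Sample size determination: SD 9, margin 10, 20 per group, alpha 5%, power 90%, clinically relevant difference 11.5. Assumed here because the plan does not say: true difference 0 for power, and a one-sided level of either 2.5% or 5%. The figures are for a plain two-group comparison of means; a repeated-measures model would shift them somewhat.

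**1. The plan's own figure.** n per group = 2 × SD² × (z for alpha + z for power)² / margin².
- One-sided 2.5%: 2 × 81 × (1.960 + 1.282)² / 100 = 17.02, so 18 (19 with the t distribution).
- One-sided 5%: 2 × 81 × (1.645 + 1.282)² / 100 = 13.87, so 14 (15 with t).
- Equivalence, two one-sided tests at 5% each: 2 × 81 × (1.645 + 1.645)² / 100 = 17.53, so 18 (19 with t).

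The stated 20 is close to the first and third. It fits a procedure that compares a confidence limit with the margin.

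**2. Standard error.** 9 × √(2/20) = 2.85.

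**3. The written rule applied to the estimate** (pass if the observed deficit is at most 10).
- True deficit 10: the estimate is equally likely to fall on either side of the margin, so P(pass) = 50%, whatever the SD or sample size.
- True deficit 11.5: Φ((10 − 11.5)/2.85) = Φ(−0.527) = 0.299, about 30% (28% at 24 per group).
- True difference 0: 2Φ(10/2.85) − 1 = 2Φ(3.51) − 1 = 99.96%, against a planned power of 90%.

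**4. A confidence-limit rule** (pass if the lower limit for repair minus reconstruction is above −10), t distribution with 38 degrees of freedom.

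| | Written rule | One-sided 2.5% | One-sided 5% |
|---|---|---|---|
| Largest observed deficit that passes | 10 | 10 − 2.024 × 2.846 = 4.2 | 10 − 1.686 × 2.846 = 5.2 |
| P(pass), true deficit 10 | 50% | 2.5% | 5% |
| P(pass), true deficit 11.5 | 30% | 0.7% | 1.5% |
| P(pass), true difference 0 | 99.96% | 92.8% | 96.4% |

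**5. The other possible reading.** Suppose non-inferiority is rejected only when a deficit above 10 is statistically demonstrated. Non-inferiority is then the default. A repair truly 10 points worse passes 97.5% or 95% of the time (one-sided 2.5% or 5%), and one truly 11.5 points worse about 93% or 87%. This reading is more permissive still.

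**The case against.** The best defence is that this is a condensed article. The rule does not say that the 10 points refer to the point estimate, and a sample size of 20 per group suggests that a proper test was intended. The level and sidedness of an interval are often left to an analysis plan. Part of this stands: the 50% figure is what the sentence yields when applied literally to the estimate, and is not an error rate the plan announces. But the article does not stay silent on the rule. It states one, and a later plan would have to replace that sentence rather than add to it. Neither reading in the working controls the error at the margin.

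A reader might infer three stronger points, which the document does not support.

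- **That any visit could decide non-inferiority**, because the section also mentions comparisons "as well as differences between the groups at each follow-up". The Abstract, the Background and Main study parameter/endpoint all place the primary objective at 1 year, and the surgical section refers to the primary outcome at that time. Analysing other visits does not make them decisive.
- **That a large benefit of repair would count as failure**, because the rule has no direction. The aim is one-directional in the Background and in Main study parameter/endpoint, and a superiority step follows. The wording is loose, but this outcome is not a realistic reading.
- **That observed deficits above 4.2 points must fail.** That cut-off assumes a one-sided 2.5% level. At one-sided 5% it is 5.2, and the plan does not say which applies.

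**Conclusion.** The concern holds in this form: the decision rule gives the 10-point margin without a confidence limit or alpha, and so conflicts with a sample size that presupposes a test against that margin. Applied literally to the estimate, it passes a repair truly 10 points worse half the time. It passes one worse by the plan's own clinically relevant 11.5 points about 30% of the time. A confidence-limit rule would hold these rates to 2.5% or 5%, and to 0.7% or 1.5%.

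The 50% rests only on the literal reading and on symmetry of the estimate. The 30% and the cut-offs also need SD 9 and 20 per group. The missing direction is secondary. Because the sentence determines the trial's main conclusion, it must be corrected before the 1-year analysis.

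**What to change.** Replace the sentence with wording such as: *Repair is non-inferior if the lower confidence limit for the mean difference, repair minus reconstruction, in IKDC Subjective score at 1 year lies above −10. Superiority is concluded if the lower limit of the two-sided 95% interval also lies above 0.* State the level of the non-inferiority limit: either two-sided 95%, or the one-sided level used in the sample size calculation. Give the same level in Sample size determination. This wording also settles the direction.

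Take the interval from the mixed model. If the data are non-normal, use a method that still gives an interval to compare with −10, for example a bootstrap or Hodges-Lehmann interval. A Mann-Whitney p-value alone cannot be set against the margin.

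The cost is one paragraph of text. No patients are added: with SD 9 and a true difference of 0, power at 20 per group is about 93% (one-sided 2.5%) or 96% (one-sided 5%). With 20% loss from 24 per group (24 × 0.8 = 19.2, so 19), it is 91.5% or 95.7%.

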### Statistics

The identified data will be entered into and analysed with SPSS version 23 (IBM SPSS, Chicago, Illinois, USA) by the trialcoordinator who is not involved in data collection and therefore not blinded to group allocation of participants. Trial results will be published in scientific journals.

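### The observed distribution decides the primary method, and the non-normal branch, as worded, does not address the 10-point non-inferiority margin

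*Protocol article*

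**What the plan says.** Under Main study parameter/endpoint the aim is stated as: "The primary objective of this non-inferiority study is to determine whether ACL repair will result in at least equal effectiveness compared with ACL reconstruction", measured by the IKDC Subjective score 1 year after surgery.

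Sample size determination works on means. It opens with "In order to detect non-inferiority of ACL repair compared to ACL reconstruction surgery", sets out "to achieve a power of 90% and an alpha of 5"%, says "it seems relevant to consider a standard deviation at nine in both groups", adds "The margin of equivalence 10 lies within this clinically relevant effect size", and concludes that "a sample size of 20 patients in each study group is required". With 20% loss to follow-up, 24 per arm are enrolled.

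Primary study parameter rejects non-inferiority if the arms differ by more than 10 points. It then splits the method by distribution: a repeated-measures mixed model for normal data, and otherwise "In case of non-normally distributed data, the Friedman test for differences within groups, and Mann-Whitney Y test for differences between groups, will be used".

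The only named normality check, Shapiro-Wilk with histograms, appears under Descriptive statistics. Under Statistics, the data are entered and analysed "by the trialcoordinator who is not involved in data collection and therefore not blinded to group allocation of participants".

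**The concern.** Three things come together in the text that governs the primary conclusion.

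- **The fallback answers another question.** A Mann-Whitney test for differences between groups has equality as its null hypothesis. Non-inferiority needs the null that repair is at least 10 points worse, or equivalently an interval in IKDC points that excludes -10. The non-normal branch offers neither, and failing to find a difference is not evidence of non-inferiority.
- **Information is lost.** The mixed model uses every observed visit. A Mann-Whitney test at 1 year uses only patients seen then.
- **The choice depends on the data and is made with the arms known.** The reason given for the missing masking does not follow: someone outside data collection is not for that reason unblinded.

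At stake is whether the trial, if its data are judged non-normal, can make the claim it was designed to make.

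**Working it through.** **Inputs from the protocol article.** Margin 10, SD 9, power 90%, alpha 5% (sidedness not given), 20 evaluable and 24 enrolled per arm, 20% loss.

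**Assumptions.** True difference 0 for power; skewed scores equal to 100 minus a gamma variable with SD 9, because the article gives no mean or shape; Shapiro-Wilk applied to each arm at 5%; a decision rule for the Mann-Whitney branch, discussed in step 4.

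**1. The plan's own figure.** n per arm = 2[SD(z₁₋α + z₁₋β)/margin]².
- One-sided 2.5%: 2[9(1.960 + 1.282)/10]² = 17.02, rounded up to 18. With the t distribution, 18 gives 89.9% power, 19 gives 91.5% and 20 gives 92.8%. The stated 20 is reproduced to within two patients.
- One-sided 5%: 2[9(1.645 + 1.282)/10]² = 13.9, so 14, which does not reproduce it.

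The design was therefore sized for a mean difference set against a margin.

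**2. Equality test and margin test side by side.** With 20 per arm the standard error is 9 × √(2/20) = 2.85, and the 95% half-width is 2.024 × 2.85 = 5.8 points. A t-based test of equality is non-significant when the observed difference lies within ±5.8. Non-inferiority is shown only when it exceeds -10 + 5.8 = -4.2. Observed differences between -5.8 and -4.2 are non-significant without showing non-inferiority.

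**3. How often the switch would occur.** Simulation, 20 per arm, 4,000 to 8,000 trials per setting, rounded:

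| Assumed scores | Shapiro-Wilk rejects in either arm |
|---|---|
| Normal | 10% |
| Skewed, mean 75 | 32% |
| Skewed, mean 80 | 43–44% |
| Skewed, mean 83 | 54% |
| Skewed, mean 85 | 64% |
| Skewed, mean 87 | 76–77% |
| Skewed, mean 90 | 94% |

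**4. Error at a true 10-point deficit, where a pass is false.** Suppose Mann-Whitney p ≥ 0.05 were taken as non-inferiority.
- Normal data: 8.5%. The t-test analogue is 1 - 0.928 = 7.2%, which agrees with step 2.
- Skewed data, means 80 to 90: about 2–6% (4.6% at mean 85). At mean 75, close to normal, a check run gave about 7%.
- Nominal: 2.5%.

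**5. Does non-normality force a switch?** No. The t-based test against -10 has simulated power of 91–94% at a true difference of 0, and a false-pass rate of 2–3% at a true deficit of 10, under normal data and every skewed shape above. A Mann-Whitney test shifted by 10 points also holds its error (2.4% normal, 2.6% at mean 85), with power of 92% and 96%.

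**6. Patients used.** At 20% loss, 24 × 0.8 = 19.2 per arm are seen at 1 year. The other 4.8 or so per arm contribute nothing to a 1-year Mann-Whitney test, but their earlier visits still enter the mixed model.

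**The case against.** Several points count against a harsher reading, and most of them stand.

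- **Rank methods can test a margin.** A reader might infer that the fallback is incapable of it. Step 5 shows otherwise, and a Hodges-Lehmann interval would also serve. What holds is narrower: the test as worded is not of that kind. A fuller document might say how an interval is obtained, but the switch itself is fixed in this text.
- **The protocol nowhere equates non-significance with non-inferiority.** Its only stated rule is the difference of more than 10 points, placed before both branches. Step 4 therefore shows what one natural reading would do, not what the plan prescribes. The stated rule does not rescue the fallback, because no interval is attached to it.
- **Pass rates inside the margin are not errors.** At a true 5-point deficit Mann-Whitney is non-significant in 62% (normal) or 52% (skewed, mean 85) of trials, which a reader might take for false conclusions. Repair is then truly non-inferior by the plan's margin, and the t-based margin test itself passes in 41% and 42%.
- **The switch is not shown to be likely.** Its frequency follows the assumed mean, and the use of Shapiro-Wilk for the primary outcome is itself inferred.
- **Friedman is a within-group test.** Its need for complete visits does not touch the between-arm conclusion. The plan also contacts no-shows to limit missing visits.
- **Coding the arms would not reliably mask the coordinator.** The same person enters the data, and items such as quality of the repair reveal the arm.

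**Conclusion.** The point holds in this form: the primary method depends on the observed distribution, the analyst knows the arms, and the non-normal branch as worded tests equality, gives nothing to compare with 10 points and discards incomplete follow-up.

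The numerical size is moderate and conditional. The false-pass rate at the margin rises from 2.5% to at most about 9%, and only under a decision rule the protocol does not state. The chance of reaching that branch runs from about 10% to 94% depending on the assumed shape and mean. The firmer conclusion needs no decision rule: if the branch is used as written, it does not answer the stated question, while a margin-based mean comparison behaves properly under all the shapes examined. Non-normality gives no reason to switch. The simulations used a simple two-sample t test, not the full mixed model.

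**What to change.** In Primary study parameter, state that the primary analysis is the repeated-measures mixed model, and that the 1-year between-group difference (repair minus reconstruction) with its two-sided 95% CI is compared with -10 whatever the normality check shows. Delete Friedman and Mann-Whitney as the primary fallback. As sensitivity analysis, report a bootstrap CI for the mean difference, or the Hodges-Lehmann shift with its CI, against the same -10.

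Correct the reasoning about the unblinded coordinator. Supplying the arms as A/B is optional, and would achieve masking only if data entry were separated from analysis.

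Cost: a change of wording and one extra sensitivity analysis. No patients are added and the sample size is unchanged.

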#### Secondary study parameters

For IKDC 2000, KOOS, Tegner, VAS, IKDC 2000 physical examination, AP-laxity, LSI for jump tests, isokinetic quadriceps and hamstring force as well as re-rupture, the same statistics as described above will be used. Re-rupture of 10% or more is considered to be clinically relevant. For the sport-specific fatigue protocol repeated measures ANOVA with SIDAK t-test post hoc test will be performed.

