### Secondary study parameters

Secondary outcomes of this study are: to determine any between group differences in self-reported functional outcomes, clinimetrics and development of osteoarthritis at 6 week, 3, 6 and 9 months, 2, 5 and 10 years after surgery and secondly, whether between groups differences exist, both with respect to perioperative classification of the ACL rupture type and onset of failure of the ACL repair or reconstruction.

Differences in baseline characteristics will be recorded by the use of IKDC 2000 demographic form, IKDC 2000 Current Health, IKDC 2000 History and reported complications and side effects.

Patient self reported outcomes will assess the patients’ perceived level of functional recovery (IKDC Subjective Scale) [23–25], daily life activities (Knee Injury and Osteoarthritis Outcome Score (KOOS)) [26], level of physical activity (Tegner Activity Level) [27, 28], knee pain (Visual Analogue Scale (VAS)) and satisfaction with the outcome of surgery. Clinimetrics will be assessed by the IKDC 2000 physical examination score [23–25], including instrumented anteroposterior laxity (Rolimeter) [29–32] as well as leg symmetry index (LSI) for Gustavsson’s jump test battery and isokinetic quadriceps and hamstrings force measured by a dynamometer (Isoforce) [33].

Additional secondary outcomes are knee kinematic parameters (i.e. degree of flexion and varus/valgus angles) 1 and 2 year(s) after surgery; the jump tests will be instrumented and patients will be equipped with inertial sensors (Xsens Technologies) for these tests. Furthermore, in order to explore the role of long lasting exertion (one-hour running and pivoting protocol) on neuromuscular fatigue and knee kinematics, a sport-specific fatigue test with EMG measurement of quadriceps and hamstring activity, and inertial biomechanical sensors to measure functional biomechanical parameters (Xsens Technologies) will be performed in a subgroup 1 year after ACL suture repair.

Two independent radiologists will evaluate the Kellgren and Lawrence score for radiologic signs of osteoarthritis on anteroposterior and lateral weight baring X-rays [34].

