Failure, defined as the occurrence pathological laxity or subjective instability, or the discontinuity of the ACL suture repair or reconstruction based on MRI or arthroscopy, as well as other complications will be recorded. Also, perioperative classification of ACL rupture type (tear location (proximal, midsubstance, distal rupture), rupture pattern (single strand, two bundles, three or more strands), and synovial sheath (completely intact, > 50% intact, < 50% intact)) [20] as well as perioperative classification regarding quality of the repair (anatomical, nearly-anatomical, non-anatomical) will be assessed [35].

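### Re-rupture, a yes/no event, is sent to the methods for scores, with no risk difference, interval or onset analysis, and its 10% threshold is not defined

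*Protocol article*

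**What the plan says.** Two sections of the Protocol article share the heading Secondary study parameters, one on outcomes and one under Statistics.

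- **Outcomes section.** One secondary outcome is a between-group difference in the "onset of failure of the ACL repair or reconstruction". The event is defined there: "Failure, defined as the occurrence pathological laxity or subjective instability, or the discontinuity of the ACL suture repair or reconstruction", the last of these shown on MRI or arthroscopy.
- **Statistics, Secondary study parameters.** Re-rupture closes a list of scores, laxity, symmetry and force measures, and the threshold follows at once: "as well as re-rupture, the same statistics as described above will be used. Re-rupture of 10% or more is considered to be clinically relevant".
- **Statistics, Primary study parameter** (directly above). The first choice of method reads: "For normally distributed data mixed models analyses for repeated measures will be used". The fallback, when normality does not hold, is given as: "In case of non-normally distributed data, the Friedman test for differences within groups, and Mann-Whitney Y test for differences between groups, will be used".
- **Statistics, Descriptive statistics** (one section higher, after the sentence on baseline characteristics). Comparisons between the randomized groups use chi-square "or Fisher’s exact test for categorical variables and the Student T-test or Mann-Whitney U test for continuous variables".

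Table 1 records re-rupture at every visit from 6 weeks to 10 years. The sample size section plans 20 evaluable and 24 enrolled patients per group, with 20% loss, for the IKDC score only.

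**The concern.** Whether a graft or repair has failed is a yes/no event with a date. Choosing its analysis by whether the data are normally distributed has no meaning for a 0/1 variable. The methods in the Primary study parameter section were written for scores: they yield no risk difference and no confidence interval, and they do not use the time of the event or deal with patients lost before it over ten years. The outcomes section speaks of failure, which can occur through laxity or instability without discontinuity, while the analysis section names only re-rupture.

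The 10% threshold is the only guide to interpretation given for this outcome. Without a stated quantity, time point or interval, two readers could apply it to the same data and disagree. Failure is the complication on which the Background compares repair with reconstruction, so an ambiguous result here would matter.

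**Working it through.** **Inputs.** Group sizes of 20 and 24 come from the sample size section. Rates come from the Background: re-rupture after reconstruction 3% to 22% within 2 years; failure after repair 4% at 2 years in the larger cohort, and 1/10 at 2 years and 2/10 at 5 years in the pilot. The true rates of 4%, 10%, 15% and 20% used below are assumptions within that range.

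**1. The plan's own figure.** No figure is given for re-rupture. For IKDC, with margin 10, SD 9, 90% power and one-sided 2.5% (sidedness is not stated, so this is assumed): n = 2 × 9² × (1.960 + 1.282)² / 10² = 17.02, rounded up to 18 per group. The stated 20 is close. Adding 20% gives 20 × 1.2 = 24 (dividing by 0.8 would give 25). So 20 and 24 are fair values for an arm.

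**2. Events to expect in 24 patients.** Reconstruction: 24 × 0.03 = 0.7 to 24 × 0.22 = 5.3. Repair: 24 × 0.04 = 1.0 at the cohort rate, 24 × 0.10 = 2.4 at the pilot's 2-year rate. Counts will be sparse.

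**3. Does the choice of test matter?** A 0/1 outcome is not normal, so the text would lead to Mann-Whitney. With ties corrected and no continuity correction, Mann-Whitney on 0/1 data equals Pearson's chi-square times (N − 1)/N. For 4/24 against 0/24:
- Pearson: 48 × (4 × 24 − 20 × 0)² / (4 × 44 × 24 × 24) = 4.364.
- Mann-Whitney: 4.364 × 47/48 = 4.273, p = 0.039.
- Fisher: 2 × C(24,4)/C(48,4) = 2 × 10,626/194,580, p = 0.109.

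The same table falls on opposite sides of 5%. Under Fisher, the smallest significant split against zero events is 5 to 0.

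**4. The 10% read as a per-arm rate.** In 20 patients it is reached at 2 events. In 24, 2 events are 8.3% and 3 are 12.5%. Exact (Clopper-Pearson) 95% intervals:
- 2/20: 1.2% to 31.7%
- 2/24: 1.0% to 27.0%
- 3/24: 2.7% to 32.4%
- 0/24: upper limit 1 − 0.025^(1/24) = 14.2%
- 0/20: upper limit 1 − 0.025^(1/20) = 16.8%

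Binomial probability that an arm shows 10% or more:

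| True rate | n = 20 (2+ events) | n = 24 (3+ events) |
|---|---|---|
| 4% | 19% | 7% |
| 10% | 61% | 44% |
| 20% | 93% | 89% |

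At a true 15%, an arm of 24 shows less than 10% in 28% of trials.

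**5. The 10% read as a difference.** With equal true rates, one given arm exceeds the other by 10 points or more in 10% (rates 4%), 21% (10%) or 27% (20%) of trials at n = 20, and in 3%, 11% or 18% at n = 24.

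This reading can give a different answer from step 4. For 0/24 on repair against 2/24 on reconstruction, the Wilson upper limit for 0/24 is 0.138 and the Wilson lower limit for 2/24 is 0.023. The Newcombe upper limit for repair minus reconstruction is −0.083 + √(0.138² + (0.083 − 0.023)²) = 0.067, or 6.7 points. A 10-point excess is then excluded, while the per-arm interval for 0/24 still includes 10%.

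**The case against.** Much of the case on the other side stands.

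- **The reference upward is ambiguous.** The chi-square/Fisher sentence also lies above, in the same Statistics section, and speaks of the randomized groups. It may be what was meant. But it sits under Descriptive statistics, the paired headings (primary, secondary) point to the score methods, and a bare test would still give neither an interval nor an analysis of onset.
- **The tests are not uninterpretable.** A reader might infer that score tests on 0/1 data are meaningless. They are not: Mann-Whitney is almost Pearson's chi-square, and Friedman on 0/1 data is Cochran's Q. The fault is narrower: a large-sample p-value at sparse counts, with no effect estimate. Part of the gap in step 3 is also Fisher's own conservatism: at 24 per group its actual error rate is 0.2% to 2.6% for equal true rates of 4% to 20%.
- **No decision hangs on the 10%.** A reader might infer a pass/fail rule on the observed rate. The text only calls 10% clinically relevant. The Primary study parameter section, by contrast, does attach a decision to its 10-point limit.
- **Low power is no error.** The trial is sized for IKDC alone, so low power to compare re-rupture contradicts nothing in the article.
- **An analysis plan may supply detail.** The absence of a time-to-event method would not be a finding alone. It counts here because the article states a method, and that method does not fit.

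**Conclusion.** The point holds in a limited form. A yes/no event is assigned, on the natural reading, to methods for scores. These give no risk difference or interval and leave onset of failure unaddressed. At the counts expected, the choice between an asymptotic and an exact test can reverse nominal significance (p = 0.039 against 0.109 for 4/24 and 0/24).

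The 10% threshold has no stated quantity or time point, and 2 or 3 events decide on which side of it an arm falls. A reader might go further and say that no result of this trial could exclude 10%. That is true only of a per-arm rate with an exact two-sided 95% interval. It is false for a between-group difference, and the article does not say which is meant.

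These figures assume 20 to 24 patients observed per arm and true rates within the range that the Background cites. The fault is in how the outcome is analysed and the threshold defined, not in the size of the trial.

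**What to change.** In Statistics, Secondary study parameters:

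1. Take re-rupture out of the list that shares the score methods.
2. Report re-rupture, and separately failure as the outcomes section defines it, as counts per arm with exact 95% intervals and as a risk difference with a Newcombe or exact 95% interval. If a test is wanted, name Fisher's exact test.
3. For onset, give Kaplan-Meier estimates per arm from surgery, so that patients lost to follow-up contribute until they leave.
4. State whether 10% is a per-arm rate or a between-group difference, and at which time point. Always report it with its interval and label it descriptive.

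A rule that counts 10% as excluded in a single arm only when the upper 95% limit falls below it should not be adopted: even 0/24 gives 14.2%, so no result could meet it.

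The cost is analysis wording only. No added patients, visits or measurements are needed, and statements about re-rupture become more cautious.
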